##### Effectiveness

Differences in sleep quality (Pittsburgh Sleep Quality Index, PSQI; [4]), severity of PTSD symptoms (PTSD Symptom Scale – Interview for DSM-5, PSSI-5; [12]), perceived distress (Perceived Stress Scale-10, PSS-10; [25]), and well-being (World Health Organization Well-Being Index, WHO-5; [32]). Changes in sleep characteristics over the 4-week study period (e.g., time of falling asleep; Consensus Sleep Diagry, CSD; [5]), are measured daily. Changes in digital biomarkers (electrodermal activity, pulse rate, respiratory rate, peripheral skin temperature, movement intensity, and sleep) are continuously assessed during the study period using a wearable (EmbracePlus; [10]).

##### Participants’ subjective experience

Patients’ views on the feasibility and effectiveness of the intervention and mechanisms of action for positive and/or negative effects are captured by a self-constructed qualitative interview at T1.

##### (Serious) adverse events

The study staff inquire about possible adverse events in the weekly support calls.

### Measures

#### Baseline assessment (T0)

Sociodemographic and health-related data (e.g., medication, psychotherapeutic treatment) are assessed at T0 using self-constructed items. Depression and anxiety symptoms are measured at T0 using the Patient Health Questionnaire-4 (PHQ-4; [21]). The PHQ-4 consists of four items: two items capture depressive symptoms, and two items capture anxiety symptoms. Participants are asked to rate how often they have been bothered by each symptom over the past 2 weeks using a Likert scale ranging from 0 (*not at all*) to 3 (*nearly every day*). The PHQ-4 has demonstrated strong reliability and validity as a brief screening tool for assessing symptoms of depression and anxiety (e.g., [21]).

Differences in emotion regulation are measured at T0 with the Emotion Regulation Questionnaire (ERQ; [15]). The ERQ consists of ten items, with six items assessing cognitive reappraisal and four items assessing expressive suppression. Participants rate their agreement with each item on a scale ranging from 1 (*strongly disagree*) to 7 (*strongly agree*). The ERQ has demonstrated consistent reliability and validity in clinical contexts (e.g., [15]).

#### Assessment at baseline (T0) and post-treatment (T1)

Sleep quality and disturbances in the past 2 weeks are measured with the Pittsburgh Sleep Quality Index (PSQI; [4]). The PSQI consists of 19 items grouped into seven component scores, each reflecting a different aspect of sleep quality: subjective sleep quality, sleep latency, sleep duration, sleep efficiency, sleep disturbances, use of sleep medication, and daytime dysfunction. The directionality and interpretation of scores vary across items. A total score ranging from 0 to 21 can be calculated. Higher scores indicate poorer sleep quality. The PSQI has shown good reliability and validity across several studies (e.g., [1, 4]).

PTSD symptoms are measured using the 24-item semistructured PTSD Symptom Scale – Interview for DSM-5 (PSSI-5; [12]). The PSSI-5 assesses PTSD symptoms according to DSM-5. The interview is divided into four sections: re-experiencing, avoidance, changes in cognition and mood, increased arousal and reactivity, and distress and interference. Item scores range from 0 (*not at all*) to 4 (*6 or more times a week/severe*), the ratings refer to the past month. The interviews were conducted by two research assistants which underwent comprehensive training in the interview procedures. The PSSI-5 demonstrated good validity and reliability in a sample of adults who had experienced DSM-5 Criterion A traumatic events [12].

Stress symptoms are assessed using the German adaptation of the Perceived Stress Scale-10 (PSS-10; [25]). PSS-10 items range from 1 (*never*) to 5 (*very often*), with higher scores indicating higher perceived stress. The PSS-10 has shown good reliability and validity in populations of university students and adults [20].

Well-being is measured by the World Health Organization Well-Being Index (WHO-5; [32]). The WHO-5 includes five items measuring positive psychological well-being. Each item is rated from 0 (*not present*) to 5 (*constantly present*) on a 6-point Likert scale. The WHO-5 has been shown to be a reliable and valid measurement tool in a variety of settings (e.g., [16, 27, 32]).

##### Daily assessments

Sleep characteristics are measured daily in the morning after waking up using the Consensus Sleep Diary (CSD; [5] over 4 weeks). Nine items assess the time of bedtime, time of sleep attempt, time needed to fall asleep, number of awakenings during sleep, total duration of waking up, time of final waking up, wake up time, and sleep quality. The CSD has shown good psychometric properties regarding utility and validity in sleep disorders [22].

##### Continuous assessments

Digital biomarker data are recorded continuously over 4 weeks by using the Empatica EmbracePlus wearable. The medical device was developed for research purposes and collects physiological biomarkers such as electrodermal activity, pulse rate, respiratory rate, peripheral skin temperature, movement intensity, and sleep detection.

### Sample size

We will include *N* = 30 participants. Given that the primary study aim is to assess feasibility, no formal sample size calculation was conducted, aligning with the recommendation that feasibility studies do not require sample size estimates [19]. The number of participants was limited to *N* = 30 since this is the minimum sample size needed to estimate a parameter for testing group differences [3]. This sample size meets the recommendation from Whitehead et al. [34] of a minimum of 15 participants per group when estimating the variance for a sample size calculation for a future trial designed with 90% power, two-sided 5% significance, and a medium (0.5) effect size. Interim analyses are not planned.

### Randomization

The allocation schedule for the random assignment of the individuals to two groups was generated by the randomization software DatInf RandList version 1.2 by a researcher not involved in other parts of the study. The generation of the randomization sequence took place prior to the recruitment of participants. *N* = 30 participants are randomly assigned to one of the two groups (i.e., robot intervention with breath simulation versus robot intervention without breath simulation) in a ratio of 1:1 using permuted blocks of random sizes between 2 and 6. Each random number is separately stored in a sequentially numbered, opaque and sealed envelope. Only the unblinded research assistant responsible for the randomization has access to the randomization envelopes. After the eligibility of a participant for the study has been ensured, the participant is included in the study by a research assistant, and the next available randomization number is assigned to the participant in an ascending order.

### Blinding

The study personnel assessing the study outcomes and conducting the data analysis are blinded to the treatment allocation. Participants could not be blinded due to the nature of the study.

### Statistical methods

Due to the pilot character of the study, the main analysis will be descriptive. Descriptive statistics will be computed for all outcomes assessed at T0 and T1 or daily, separately for the two groups. The means and standard deviations will be calculated for the continuous variables, and frequencies and percentages will be calculated for categorical variables. Cohen’s *d* effect sizes will be calculated for the outcomes to provide an indication of the magnitude of observed differences. We will also examine the confidence intervals around the point estimates for relevant outcomes, offering a more nuanced interpretation of the results.

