### Outcomes

#### Primary outcome

We evaluate the feasibility of the outcome data collection, focusing on randomized participants providing data at post-treatment (T1) after a 4-week Somnox 2 robot intervention with human breath simulation, or after a 4-week Somnox 2 robot intervention without breath simulation. Feasibility, set at > 50%, applies equally to both groups. This criterion considers potentially high dropouts in individuals with mental health conditions and the technical complexity of the study (e.g., using a wearable for 4 weeks).

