Another strength of this study is the inclusion of a control group. We investigate the effectiveness of the daily use of a breath robot with the daily use of the same robot without breath simulation. Such a study design allows us to investigate whether the breathing of the robot  – which is assumed to be the main mechanism of action  – is crucial for the effect of the robot intervention, if present. However, this study design cannot provide information about whether the overall robot intervention, including daily hugging of the robot with a nice texture, perception of the robot’s breathing, and listening to relaxing music, will more greatly reduce sleep problems in PTSD patients compared to no intervention.

Although both study groups receive a similar intervention and instruction, participants cannot be blinded to whether the robot is breathing. The study is therefore susceptible to participant effects. However, the study personnel assessing the results are blinded, as is the person performing the statistical analysis. Another shortcoming of this study could be seen in the fact that 30 participants are too few to detect small effects. However, this study is primarily designed to assess feasibility and not to detect intervention effects. We also followed recommendations for determining sample size in pilot trials [3, 34]. The study is further limited to examining the feasibility and effectiveness over a 4-week period, as we do not conduct follow-up measurements.

Despite these limitations, we assume that this feasibility study will gain novel insights into the application of a breath robot in PTSD patients with sleeping problems. As no previous study has been conducted on this research question, it is unclear whether patients with PTSD will accept the intervention and whether the intervention will have any positive or negative effect on sleeping problems or arousal. However, if the breath robot will be feasible and effective in this patient group, the intervention has the potential to significantly improve the treatment of PTSD. Given the shortage of psychotherapy and the often long wait times for psychotherapy, it is critical to develop alternative treatment options. Breath robots such as the Somnox 2 may be more readily available, cost less, and can be used more flexibly at home compared to psychotherapy. However, based on current empirical knowledge, there is no evidence that breath robots are effective in reducing sleep problems in patients with PTSD.

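### Statistical methods names Cohen's d for a trial of about 15 per arm, where its mean is about 3% to 6% too large in absolute size; the small-sample corrected form costs nothing

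*Protocol article*

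**What the plan says.** Statistical methods calls the main analysis descriptive. It plans group means and SDs for continuous outcomes and confidence intervals around point estimates for the relevant ones. For standardised effects it names one estimator: Cohen's d "effect sizes will be calculated for the outcomes to provide an indication of the magnitude of observed differences". It does not give the SD in the denominator or mention a small-sample correction.

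The sizes at which d will be used follow from other sections:

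- Sample size sets N = 30, and Randomization allocates "in a ratio of 1:1 using permuted blocks of random sizes between 2 and 6", which gives about 15 per arm.
- Primary outcome requires T1 data from more than 50% of those randomised, in each group. Its stated reason is "This criterion considers potentially high dropouts in individuals with mental health conditions", together with the technical demands of the study.

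Sample size is the only section that describes a later trial. It supports the pilot size with a recommended "minimum of 15 participants per group when estimating the variance for a sample size calculation for a future trial" that is "designed with 90% power, two-sided 5% significance" and has "a medium (0.5) effect size". The Discussion accepts that "30 participants are too few to detect small effects" and says that detecting effects is not the main purpose.

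**The concern.** Cohen's d divides the mean difference by an SD estimated from the same small sample. The reciprocal of an estimated SD is on average too large, so the mean of d lies further from zero than the true standardised difference. With hundreds of participants this can be ignored. With 28 degrees of freedom or fewer it is a few per cent.

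What is at stake is the accuracy of the standardised effects that the article plans to report. Effectiveness is a stated secondary aim, and the article presents the study as the first in this population, so later readers will have few other figures. A confidence interval shows how imprecise an estimate is, but it does not remove bias from the point estimate.

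**Working it through.** **Inputs.**
- N = 30, 1:1 (Sample size; Randomization). The article's own figure reproduces: 2 × 15 = 30.
- T1 data from more than 50% in each arm (Primary outcome). 8/15 = 53% passes and 7/15 = 47% fails, so 8 per arm is the smallest size that still meets the criterion. It is a lower bound, not an expected number.
- Assumptions: d uses the pooled SD of two independent, roughly normal groups, without correction. The article gives no expected effect, so true values of 0.2, 0.5 and 0.8 are used for illustration.

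**Bias factor.** With df = n1 + n2 − 2,

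E[d] = δ / J(df), where J(df) = Γ(df/2) / [√(df/2) · Γ((df − 1)/2)] ≈ 1 − 3/(4df − 1).

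J depends only on the total number analysed, so a slightly uneven split of the 30 does not change it.

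| Per arm | df | J exact | J approx. | Relative bias, 1/J − 1 | E[d] if δ = 0.5 |
|---|---|---|---|---|---|
| 15 | 28 | 0.9729 | 0.9730 | +2.8% | 0.514 |
| 12 | 22 | 0.9655 | 0.9655 | +3.6% | 0.518 |
| 10 | 18 | 0.9576 | 0.9577 | +4.4% | 0.522 |
| 8 | 14 | 0.9453 | 0.9455 | +5.8% | 0.529 |

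A simulation of 200,000 trials with 15 per arm and δ = 0.5 gave a mean d of 0.515, in agreement with the formula.

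**Size beside the sampling error.** With ñ = n1·n2/(n1 + n2),

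Var(d) = [df/(df − 2)]·(1/ñ + δ²) − (δ/J)².

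- 15 per arm, δ = 0.5: (28/26)(1/7.5 + 0.25) − 0.5139² = 0.1487, so SD = 0.386. Bias 0.0139/0.386 = 3.6% of one standard error.
- 8 per arm, δ = 0.5: (14/12)(1/4 + 0.25) − 0.5289² = 0.3036, so SD = 0.551. Bias 0.0289/0.551 = 5.3% of one standard error.

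The corresponding 95% half-widths (1.96 × SD) are 0.76 and 1.08. For true effects from 0.2 to 0.8, the absolute bias runs from 0.006 (0.2, 15 per arm) to 0.046 (0.8, 8 per arm).

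**Effect of the correction.** g = J·d has mean δ: 0.9729 × 0.5139 = 0.500 and 0.9453 × 0.5289 = 0.500. Its variance is J²·Var(d). At δ = 0.5 the mean squared error changes as follows:

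- 15 per arm: from 0.1487 + 0.0139² = 0.1489 to 0.9729² × 0.1487 = 0.1408, about 5% lower.
- 8 per arm: from 0.3036 + 0.0289² = 0.3044 to 0.9453² × 0.3036 = 0.2713, about 11% lower.

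**The case against.** The strongest case against raising this has four parts.

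**Nothing depends on it.** The primary outcome is a proportion judged against 50%, the analysis is descriptive, and confidence intervals are already planned. This stands, and it is why the point is minor.

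**The correction may be left to a fuller document.** An article need not give the SD or the correction, and some authors write Cohen's d when they mean the corrected form. This stands in part. No omission is alleged: the article names an estimator, and under its usual definition that estimator is biased at the article's own sample sizes. If a correction is already intended, the same one-line edit makes it visible.

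**The bias concerns the mean of d.** The distribution of d is right-skewed when the effect is positive. At a true 0.5 its median is about 0.50 at 15 per arm and 0.51 at 8 per arm, whereas the median of g is about 0.49 and 0.48. So d is nearly unbiased in the median, and g is slightly low. This is correct. The case for g rests on its mean and on its lower mean squared error.

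**The consequences are easily overstated.** A reader might infer that an inflated effect will be carried into the next trial and leave it too small. The article does not support this: Sample size links the pilot to estimating a variance, with the effect set beforehand at 0.5, and no section feeds the observed d into a later design. Sample-size or power losses worked out from d would therefore describe a use that is not planned. A reader might also infer that the bias always flatters the robot. It is multiplicative: it vanishes at a true effect of zero and exaggerates harm if the effect is negative, and the Discussion leaves the direction open. Larger figures for within-arm changes do not belong here either, because the article does not specify a within-arm d.

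**Conclusion.** The point holds as a small, free improvement. On average the uncorrected between-arm d overstates the absolute size of the true standardised difference by 2.8% with all 30 participants analysed and by 5.8% with 8 per arm. At a true 0.5 that is 0.014 to 0.029, against a standard error of 0.39 to 0.55. No feasibility conclusion changes, and no effect on a later trial is claimed. The result rests on three assumptions: the conventional pooled-SD definition of d, approximately normal outcomes, and no correction already intended elsewhere.

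**What to change.** In Statistical methods, replace Cohen's d with the small-sample corrected standardised mean difference, Hedges' g = J(df) × d with J ≈ 1 − 3/(4df − 1) and df = n1 + n2 − 2. State that the SD is the pooled between-arm SD, and report g with its confidence interval. Beside it, give the mean difference in points of each scale with its own confidence interval.

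The cost is one line of wording and one multiplication per outcome, with no extra participants or data. The only downside is that reported standardised effects are about 3% to 6% smaller than uncorrected ones.

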## Discussion

This pilot study will be, to our knowledge, the first randomized controlled study on the feasibility and effectiveness of a breath robot (Somnox 2) intervention to reduce sleep problems in patients with PTSD. The findings may be of particular importance as sleep problems are common in PTSD.

Few studies have examined the improvement of sleep through robotic interventions in patients with dementia. Recently, a systematic review and meta-analysis on the effects of robotic interventions to improve sleep identified four controlled studies among older adults, most of whom were diagnosed with dementia [28, 29]. The interventions had no significant effects on sleep duration compared to the control conditions. However, most of the trials were of low study quality, and all examined robot interventions not designed to improve sleep. Two additional studies not considered in the review examined the effects of a breath robot designed to improve sleep. One study examined a robotic breath intervention with *N* = 36 premature infants [17]. Infants used a “breathing” teddy bear that was adapted to the breathing pattern of the infants. The use of the breath robot for 2 weeks resulted in improved sleep quality post-intervention. One pilot RCT examined the effects of a 3-week breath robot intervention (Somnox robot) in *N* = 44 adults with insomnia [29]. No diferences in insomnia symptoms were found between the intervention and wait-list control groups. However, the study was small, and not all patients fully adhered to the intervention. The planned pilot study outlined in this protocol will add first evidence on the feasibility and effectiveness of a breath robot intervention among patients with PTSD.

A methodological strength of this study is that we follow good practice recommendations for pilot and feasibility studies [19]. We also consider the Standard Protocol Items: Recommendations for Interventional Trials (SPIRIT) checklist as a guide for reporting this study protocol. Another strength is that we diagnose PTSD using a structured clinical interview. For clinical outcomes, we use validated self-report measures that we combine with objective biomarkers assessed continuously over 4 weeks in the home environment of the patients. However, most data collected include self-reported data, which can introduce measurement error.

Another strength of this study is the inclusion of a control group. We investigate the effectiveness of the daily use of a breath robot with the daily use of the same robot without breath simulation. Such a study design allows us to investigate whether the breathing of the robot  – which is assumed to be the main mechanism of action  – is crucial for the effect of the robot intervention, if present. However, this study design cannot provide information about whether the overall robot intervention, including daily hugging of the robot with a nice texture, perception of the robot’s breathing, and listening to relaxing music, will more greatly reduce sleep problems in PTSD patients compared to no intervention.

Although both study groups receive a similar intervention and instruction, participants cannot be blinded to whether the robot is breathing. The study is therefore susceptible to participant effects. However, the study personnel assessing the results are blinded, as is the person performing the statistical analysis. Another shortcoming of this study could be seen in the fact that 30 participants are too few to detect small effects. However, this study is primarily designed to assess feasibility and not to detect intervention effects. We also followed recommendations for determining sample size in pilot trials [3, 34]. The study is further limited to examining the feasibility and effectiveness over a 4-week period, as we do not conduct follow-up measurements.

Despite these limitations, we assume that this feasibility study will gain novel insights into the application of a breath robot in PTSD patients with sleeping problems. As no previous study has been conducted on this research question, it is unclear whether patients with PTSD will accept the intervention and whether the intervention will have any positive or negative effect on sleeping problems or arousal. However, if the breath robot will be feasible and effective in this patient group, the intervention has the potential to significantly improve the treatment of PTSD. Given the shortage of psychotherapy and the often long wait times for psychotherapy, it is critical to develop alternative treatment options. Breath robots such as the Somnox 2 may be more readily available, cost less, and can be used more flexibly at home compared to psychotherapy. However, based on current empirical knowledge, there is no evidence that breath robots are effective in reducing sleep problems in patients with PTSD.

## Data Availability

The data sets generated or analyzed during the current study are not publicly available because the trial is ongoing. After the publication of the results of this study, the respective anonymized data will be made available by the corresponding author upon reasonable request.

## Abbreviations

DSM-5: Diagnostic and statistical manual of mental disorders
PTSD: Posttraumatic stress disorder
EDA: Electrodermal activity
PRV: Pulse rate variability
RR: Respiratory rate
PR: Pulse rate
MI: Movement intensity
ST: Skin temperature
SD: Sleep detection
RCT: Randomized controlled trial
ERQ: Emotion Regulation Questionnaire
PHQ-4: Patient Health Questionnaire-4
PSSI-5: PTSD Symptom Scale – Interview for DSM-5
PSS-10: Perceived Stress Scale-10
WHO-5: World Health Organization Well-Being Index
CSD: Consensus Sleep Diary
PSQI: Pittsburgh Sleep Quality Index
SPIRIT: Standard protocol items: recommendations for interventional trials
